## Abstract

**Background:**

The global prevalence of diabetes mellitus (DM) has been increasing over recent decades. In Germany, the prevalence for DM type 1 and type 2 in adults is estimated at about 7.7%. Hence, diabetes has to be classified as a serious public health concern. Being diagnosed with DM and facing possible sequelae might have a negative impact on patients’ mental and physical well-being. However, diabetes not only affects patients themselves, but also their close relatives. To improve the quality of life for patients and relatives alike, the German Association of Diabetes Nurses and Education experts (VDBD) elaborated the first education program tailor-made for relatives of diabetes patients. This article describes the concept and design of the trial evaluating the efficacy of this education program called “Dia*Life*—Living Together with Diabetes”.

**Methods:**

This evaluation study is a cluster randomized controlled trial, in which the study centers will be randomly assigned either to the intervention group or the control group. Study centers will recruit relatives of and patients with DM type 1 and type 2. Members of the intervention group will participate in the education program Dia*Life*, whereas participants randomized in the control group will act as waiting-list controls. The study will assess the efficacy of Dia*Life* by comparing diabetes-related knowledge between the intervention and control groups as the primary outcome for participants. As the primary outcome in patients, the Hba1c value will be assessed. In addition, diabetes-related distress, family interaction, and other secondary endpoints will be considered as secondary outcomes. Long-term efficacy will be assessed 6 and 12 months after intervention. Hierarchical regression models will be used to analyze effects over time.

**Discussion:**

While there is scientific evidence for the efficacy of education programs addressed to (diabetes) patients, there is a research gap with regard to intervention studies evaluating the efficacy of education programs designed for patients’ relatives. The study results will provide information on the efficacy of the Dia*Life* education program. In addition, factors that might hinder a successful implementation of an education program for relatives will be identified.

**Trial registration:**

German Clinical Trials Register, DRKS00015157. Registered on 24 August 2018.

**Electronic supplementary material:**

The online version of this article (10.1186/s13063-019-3600-4) contains supplementary material, which is available to authorized users.

## Background

Today, the number of adults diagnosed with diabetes mellitus (DM) is estimated at around 7.7% of the German population [1]. When adding the number of undiagnosed cases, the total number of adults who are affected by diabetes and its health-related, financial, and psycho-social consequences can amount to 6.7 million [2].

Effective self-management of diabetes can contribute substantially to successful therapy. Since education programs for diabetes patients are considered to have an overall positive effect [3], they are viewed as a fundamental component of diabetes therapy [4]. Education programs are structurally embedded in Disease Management Programs (DMBs) of health insurance providers and are required by the evidence-based national guidelines of diabetes management [5]. In 2016, the German federal insurance office had certified 20 different education programs for people affected by diabetes mellitus type 1 or type 2 [6, 7], but no education program was specifically designed for patients’ relatives. In the following we will show why and how an education program for relatives of patients with diabetes might benefit the patients and relatives likewise.

First, diabetes has an enormous impact not only on the daily life of patients, but also on the daily life of their relatives. The DAWN 2 Study, a worldwide study regarding psycho-social aspects in diabetes treatment, revealed that psychological, financial, and emotional strains caused by DM equally affect patients and relatives [8, 9]. Kulzer et al. [9] showed, for instance, that relatives are equally affected by diabetes-related stress and strains. However, they did not report whether relatives of patients with diabetes mellitus type 1 or type 2 perceive the diabetes-related stress and strains differently. Moreover, they showed that relatives are more afraid of (nocturnal) hypoglycemia than the patients themselves [3, 9].

Second, Kulzer et al. [9] found that one-third of relatives stated to feel frustrated as they did not know how to support or help the patient. Further, they showed that the discrepancy between this lack of knowledge, on the one hand, and the wish to support the patient, on the other, often leads to miscommunication and interpersonal conflicts. The social support of relatives is perceived differently by the patients depending how the support is communicated and provided. At worst, patients perceive the support as paternalism and criticism. There is also some evidence for adolescent patients that family social support predicts higher adherence to treatment and higher quality of life, whereas conflicts within the family decreases the quality of life in patients [10]. However, to address these sources of interpersonal conflicts, Kulzer et al. [9] came to the conclusion that an education program for relatives of diabetes patients might benefit the relatives and the patients equally and might improve their quality of life. The education program developed contains social–psychological modules to show relatives an adequate way to express their support, concerns, and feelings in a more constructive and less criticizing way.

Third, an education program for relatives of diabetes patients might improve the quality of care, particularly in light of demographic changes. Effective diabetes self-management might decrease with higher age and higher disease burden [11]. Implementing an education program tailor-made for relatives aims to enable relatives to compensate patients’ potential (cognitive) impairment caused by old age. Since patients’ spouses also become older, Dia*Life* is an education program that is also addressed to (younger) family members alike. Moreover, an education program for relatives can also support patients with an immigrant background, who might be impaired by language barriers and would therefore not participate in an education program themselves.

This evaluation study will investigate the efficacy of an education program developed for relatives of diabetes patients. A positive scientific evaluation of the education program is required for a certification application at the responsible German federal authority. The certification, in turn, is a prerequisite for reimbursement by health insurances.

## Development of an education program for relatives

Against this background, in 2016 the German Association of Diabetes Nurses and Education Experts (Verband der Diabetes-Beratungs- und Schulungsberufe in Deutschland e.V. (VDBD)) initiated the development of an education program for relatives of diabetes patients funded by the German Federal Ministry of Health. This education program is called Dia*Life.* Within the Dia*Life* program, relatives will be trained personally in groups by certificated diabetes educators (CDEs). After analyzing existing education programs addressed to diabetes patients, focus group interviews with relatives of diabetes patients were conducted, in which we assessed inter-alia skills and topics they would like to learn. Based on these results, experts in diabetes care were also interviewed to check whether they would identify the same possible main themes to be included in an education program for relatives from their experiences in everyday practice.

In addition, a quantitative survey among relatives and diabetes care experts was conducted (*n* = 82 relatives and *n* = 120 experts (*n* = 4 physicians, *n* = 116 diabetes educators)) in which participants were asked to rate the relevance of different topics for a relatives-centered education program.

Based on this described explorative study, the structure and content of Dia*Life* were developed. The first draft of Dia*Life* was tested in 2017 in a pilot study that assessed its comprehensibility and applicability. In this pilot study, two CDEs were asked to educate independently the relatives of diabetes patients. Both CDEs and participating relatives evaluated the education program using standardized evaluation forms as developed by the study team. All in all, the Dia*Life* education program was perceived as comprehensible by the participants and also by the CDEs. However, the results of this evaluation, such as suggestions for improvement, were taken into account in the final version of the Dia*Life* program.

## Methods and design

In order to examine the efficacy of Dia*Life*, a cluster randomized controlled trial (cRCT) will be conducted involving an intervention group and a control group. The cRCT will investigate the efficacy of the Dia*Life* program by comparing inter-alia diabetes-related knowledge between the intervention and control groups (parallel groups). Therefore, relatives of people diagnosed with diabetes mellitus type 1 or type 2 will be assigned to an intervention or to a waiting list condition (control group).

### Power calculation and sample size

Following the study by Pieber et al. [12], efficacy of an education program such as the Dia*Life* program would be confirmed if an effect size of 29% (of correct answers of questions assessing diabetes-related knowledge) between the groups could be identified. To reach a sufficient power of 90%, it is necessary to include 12 relatives in the intervention group and in the control group. However, when presuming a drop-out rate of 10%, 14 relatives per group need to be included. It is assumed that data will correlate within study centers. Therefore, correction in the form of design-effect will be made [13]. In a comparable study (cluster randomized trial: ISDM), an intra-class correlation (ICC) of 0.21 was assessed [14, 15]. By including 11 relatives per study center, the design-effect will be: DE = 1 + (*m* – 1) ICC = 3.1. Thus, by correcting with the design-effect (DE = 3.1), an increased number of cases of 44 participants per group is required (i.e. *n* = 44 participants per group for type 1 and type 2 in the intervention group, n = 44 participants per group for type 1 and type 2 in the control group).

The study will be conducted in varying study centers all over Germany. In order to secure the sufficient number of cases, eight education programs with 11 relatives per diabetes type must be executed (overall, 16 education programs). Therefore, the aim is to recruit 44 relatives plus their affected patients per diabetes group (type 1 and type 2). Overall, a number of cases of 176 relatives and 176 patients is required (in total, *n* = 352).

### Recruitment and preparation

#### Recruitment of study centers

The VDBD has an established network of healthcare professionals specialized in the treatment of diabetes. With the help of this network, the study team will contact eligible study centers and will invite them to participate. The aim is to recruit at least 16 study centers in Germany, which will be assigned randomly to either the intervention or the control group. Each study center has to designate a qualified certified diabetes educator (CDE) and will recruit relatives and patients of both types of diabetes. For this purpose, the study team will provide flyers and other recruitment material. Moreover, research assistants will give study centers explanatory instructions by telephone regarding the recruitment material and the recruitment process. Furthermore, study centers will be provided with all education program materials, consisting of trainer manuals, presentation slides, worksheets, handouts, and other teaching material. Before the study starts, the designated CDEs will be trained in how to use Dia*Life* and its materials by the study team. Within these Train-the-Trainer sessions, the structure and organization of the cRCT will also be explained.

#### Recruitment of participating relatives and patients

Relatives and patients will be recruited according to the inclusion and exclusion criteria. Overall, 176 relatives and 176 patients will be recruited, divided into four groups (Table 1). At the time of recruitment, what type of diabetes mellitus the patient has will be assessed according to their patient file. Participating relatives and patients will be subsequently categorized into the groups. Recruited relatives and patients are in either the intervention or the control group, depending on their study center’s allocation. Relatives and patients will receive detailed information sheets and must give their written consent in order to participate. The designated CDE will collect the declarations of consent and will send them to the study team.

**Table 1 Tab1:** Assignment of participants into groups

	Intervention group	Control group
Diabetes mellitus type 1	Relatives *n* = 44	Relatives *n* = 44
	Patients *n* = 44	Patients *n* = 44
Diabetes mellitus type 2	Relatives *n* = 44	Relatives *n* = 44
	Patients *n* = 44	Patients *n* = 44

### Eligibility criteria

Table 2 lists the inclusion and exclusion criteria for the study centers, participating relatives, and participating patients.

**Table 2 Tab2:** Criteria for inclusion and exclusion

	Criteria for inclusion	Criteria for exclusion
Study center	• Suitable premises and technical equipment • Located in Germany • Designation of a certified diabetes educator (CDE) with adequate expertise in diabetes management • CDE’s participation in the Train-the-Trainer program	• Healthcare facilities specializing in the treatment of diabetes in hospitals
Participating relatives	• Relatives of patients with diagnosed diabetes mellitus type 1 or type 2 • Spouses, partners, or family members who live together with the diabetes patient • Aged at least 18 years	• Dementia or other severe cognitive or physical diseases, which impede regular attendance • Insufficient level of German • Shift work • More than one close relative suffering from diabetes • Relatives who are themselves diagnosed with diabetes mellitus
Participating patients	• Aged at least 18 years	• Inability to fill out the questionnaires • Insufficient level of German

#### Eligibility criteria of study centers

Eligible German healthcare facilities have to provide suitable premises and technical equipment to carry out the education program. Furthermore, study centers have to designate a CDE whose level of expertise in diabetes management (medical and didactical knowledge) is adequate to train relatives in Dia*Life* and who participated in the Train-the-Trainer program. We decided to exclude healthcare facilities specializing in the treatment of diabetes in hospitals since in these facilities only emergency cases are treated. In these cases, it is uncertain how long patients will stay and, thus, whether their relatives could compete the Dia*Life* education program. A list of recruited study centers can be obtained on request.

#### Eligibility criteria of relatives of patients with diabetes mellitus

Recruited relatives of patients diagnosed with diabetes mellitus type 1 or type 2 must meet the following criteria: participants must be at least 18 years old and must live together with the patient. Relatives who are themselves affected cannot be included. Furthermore, relatives suffering from dementia or another cognitively restricting disease, which might impede regular attendance, cannot be included. Insufficient German skills or shift work are further exclusion criteria for relatives.

#### Eligibility criteria of patients with diabetes mellitus

The participating patient should be the only (close) relative with diabetes mellitus in the family and must also be at least 18 years old. Patients with a severe cognitively restricting disease must be excluded since the completion of questionnaires might be impaired.

### Intervention scheme

Dia*Life* is a structured modular education program and consists of mandatory and elective modules. Each module lasts approximately 90–120 min. Modules have been adjusted to the specific type of diabetes mellitus, resulting in some content-related differences. Due to this fact, two versions of Dia*Life* are available: one version addresses relatives of persons with type 1 diabetes; the other has been designed for relatives of persons with type 2 diabetes (Table 3). The Dia*Life* education program for type 1 consists of nine modules, whereas the curriculum for type 2 diabetes consists of eight modules. In the curriculum for type 1 diabetes, the module “diabetes-associated conditions” was added, since the topic is particularly important for this target group. However, the topic is also part of the program for type 2 diabetes, in which it was integrated into the module “fundamental principles of diabetes type 2”.

**Table 3 Tab3:** Mandatory and elective modules of the Dia*Life* education program

	Diabetes mellitus type 1	Diabetes mellitus type 2
Mandatory modules	• Fundamental principles of diabetes type 1	• Fundamental principles of diabetes type 2
	• Understanding the impact of diabetes on daily life	• Understanding the impact of diabetes on daily life
	• Emergency situations	• Emergency situations
	• Insulin therapy	• Diet and exercise
	• Strategies of communication	• Strategies of communication
Elective modules	• Understanding dementia and its consequences	• Understanding dementia and its consequences
	• Diet and exercise	• Insulin therapy
	• Special situations	• Special situations
	• Diabetes-associated conditions	

Relatives of the intervention group will complete the Dia*Life* education program in the version for the patient’s diabetes type. The group size for the educational intervention is set to a minimum of three relatives and to a maximum of six. Within the study, every mandatory and elective module will be taught by the CDE in their medical practice. It is intended to teach one Dia*Life* module per week, which means that the whole education program would take 8 or 9 weeks, respectively. However, since CDEs are challenged by a heavy workload, they can freely choose how many modules to schedule per week, but will be asked to complete the whole program in a maximum of 9 weeks. Relatives of patients with type 1 diabetes will attend nine modules overall, which are equivalent to an attendance time of at least 13.5 h up to 18 h. The program for relatives of patients with diabetes type 2 contains eight modules. Thus, the required attendance time is estimated at least 12 h up to 16 h. After recruitment, participating relatives will receive a schedule with course dates from their study center. The educational intervention will consist of lectures given by the CDE as well as (group) tasks, exercises, and discussions, which are all explained in detail in the trainer manual. Additionally, after completion of a module, participants will receive handouts with a summary of the most important topic-related information. After completing the educational intervention, the participants are expected to have extended diabetes-related knowledge, coping strategies, and improved communication skills. Furthermore, the education program should empower relatives regarding diabetes care.

In contrast, participating relatives of the control group will not attend the Dia*Life* program during the study, but will be assigned to a waiting list. As soon as the study is completed, participating relatives of the control group will be invited to attend the Dia*Life* education program. Consequently, all study participants will have the possibility to attend the education program regardless of group assignment, but at different points of time. Until relatives of the control group are invited to the Dia*Life* education program, they will receive no specialized training but will be involved in the management of the patient’s disease as before.

### Study design

To evaluate Dia*Life*, a mixed-method approach consisting of both a quantitative survey and a qualitative survey will be applied. In the following, both approaches will be explained in detail. A flow diagram of the study’s structure is shown in Fig. 1.

**Fig. 1 Fig1:**
[figure not shown]
Cluster-randomized trial intervention scheme

#### Quantitative assessment

All relatives and patients will be asked to complete questionnaires at four different times, with baseline assessment at recruitment. Participants assigned to the intervention group will fill out a second questionnaire (follow-up 1) after completing the implemented intervention. Participants in the control group will also fill out a second questionnaire after an interval of approximately 8 weeks. In both groups, the second and third follow-ups will take place 6 and 12 months after follow-up 1, respectively. Parallel to all four moments of assessment, participating CDEs will be asked to complete a questionnaire for each patient in order to ascertain patients’ current health condition, their latest recorded Hba1c value, and their current diabetes treatment. Participants will be invited to all four assessments by postal reminder.

The data input will be performed successively. As soon as missing data are noticed, the study team will contact the corresponding CDE. The CDE will be asked to contact and remind the participants to provide missing data. The CDEs are also asked to report any drop-out as soon as it occurs.

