### Randomization and blinding

Study centers in the form of practices specialized in diabetes will be sequentially allocated at a ratio of 1:1 and stratified by diabetes type to either the intervention or control group by randomization. The randomization sequence will be generated by the Centre of Clinical Studies at the University Hospital Jena. Given the need to assign an equal number of study centers randomly to the intervention or control group, a computer-based block randomization will be applied [17] using nQuery 7.0.

Given that the study team has to inform study centers if they are going to train relatives within or after the study, it is not possible to blind the study centers. After signing the cooperation contract, the study centers will be randomized and informed about group allocation. The study centers will subsequently receive recruitment material, consent forms for patients, and other materials (e.g. questionnaires) by postal mail. Materials do not vary between the intervention and control groups. Participants will not know their group affiliation at the time of recruitment, but will know about it after giving written consent. The statistician concerned with randomization and data analysis will not be involved in other study-related assignments. Allocation concealment will be ensured for statistical analyses. The research team will remain blinded to the results until data collection is completed.

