### Primary outcomes

#### Participating relatives

Difference in knowledge about diabetes between relatives of the intervention and control groups was determined as the study’s primary endpoint. Participants will be asked to answer knowledge-based questions before and after intervention (intervention group) or during regular consultation and care (control group). Result examination focuses on the question regarding if and to what extent knowledge has increased after the implemented intervention. Therefore, two questionnaires assessing relatives’ knowledge about diabetes type 1 or type 2 will be applied. These questionnaires will be developed following the templates used by Kronsbein et al. [18], that have already been applied by Pieber et al. [12]. Both questionnaires will consist of 16 questions regarding, for example, the impact of insulin on blood glucose, symptoms, causes and treatment of hypoglycemia and hyperglycemia, diabetes-related comorbidities, blood glucose monitoring, and impact of certain foods on the blood glucose level. In addition, the questionnaire for relatives of patients suffering from diabetes type 1 includes questions about glucagon shots, symptoms and treatment of ketoacidosis, and carbohydrate units. Relatives of patients with diabetes type 2 are additionally asked about the impact of certain factors (e.g. eating behavior) on blood glucose and what kind of preventive medical checkups are generally advised. The questionnaires used are available upon request from the authors. A translated version of the questionnaire is available in Additional files 2 and 3.

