### Data collection and data management

Within the quantitative elicitation, data will be collected using questionnaires. Therefore, participants will be invited by postal mail to visit their respective study center in order to fill out the questionnaires. The study centers will then send the questionnaires back to the study team in a prepaid return envelope. To ensure high follow-up rates, participating relatives receive a monetary incentive of €50 after the completion of the last questionnaire. After every follow-up period, a trial manager will check whether data and study documents are complete. Data monitoring will be independent of the sponsor. Figure 2 shows the schedule of enrolment, interventions, and assessments according to recommendations for interventional trials (SPIRIT). A SPIRIT checklist is presented in Additional file 1.

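### Missing data are chased through the unblinded educator with no exemption for the knowledge test, so blank items on the relatives' primary endpoint can be filled in after the sitting

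*Protocol article*

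**What the plan says.** All places are in the protocol article.

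- **Quantitative assessment.** Data are entered as they arrive. "As soon as missing data are noticed, the study team will contact the corresponding CDE", and then: "The CDE will be asked to contact and remind the participants to provide missing data". No instrument is excluded. Drop-outs are dealt with in a separate sentence.
- **Primary outcomes, Participating relatives.** The relatives' primary endpoint is the difference between arms in diabetes knowledge, measured with a 16-question test in a type 1 or a type 2 version.
- **Intervention scheme.** In the intervention arm "every mandatory and elective module will be taught by the CDE in their medical practice". After each module "participants will receive handouts with a summary of the most important topic-related information". Control relatives wait until the study is over; until then "they will receive no specialized training but will be involved in the management of the patient’s disease as before".
- **Randomization and blinding.** Because centers must be told when they will teach, "it is not possible to blind the study centers".
- **Data collection and data management.** Participants fill in the questionnaires at their center. "The study centers will then send the questionnaires back to the study team in a prepaid return envelope". A trial manager checks completeness after every follow-up period.
- **Recruitment of study centers, and Table 2.** Centers receive the full set of program materials, and the CDE's attendance at the trainer course is an inclusion criterion for every center, whatever its later allocation.
- **Handling of missing data.** Only a general commitment to suitable techniques is given.

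**The concern.** On most instruments an unanswered item is a gap, and asking for it again is good practice. On a knowledge test a blank may itself be the result: the relative did not know. Reopening it after the sitting exchanges that result for an answer given under other conditions, when it can be looked up or talked through. The person asked to prompt for it knows the allocation and, in one arm, has taught the content. Relatives in that arm also have written summaries of it, which control relatives do not have. A retrieval step that looks the same in both arms can therefore work differently in each.

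At stake is whether the primary comparison measures unaided knowledge. The weakness lies in how data are collected. An analysis plan could say how blanks are scored, but it cannot restore a blank already overwritten unless retrieved answers are marked as such.

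**Working it through.** **1. The plan's own figures, reproduced for scale.** Inputs from Power calculation and sample size: target difference 29 points of correct answers, power 90%, 12 per group, 10% drop-out, ICC 0.21, 11 relatives per center.

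- Drop-out: 12 / 0.90 = 13.3, rounded up to 14.
- Design effect: 1 + (11 − 1) × 0.21 = 3.1.
- Per group and diabetes type: 14 × 3.1 = 43.4, rounded up to 44; 4 × 44 = 176 relatives.

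These agree with the article and are not in dispute here.

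**2. What one item is worth.** Assuming equal weights (the scoring is not shown), one item is 100 / 16 = 6.25 points. The target of 29 points is 29 / 6.25 = 4.64 items.

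**3. Shift caused by retrieval.** Let b be the number of blanks chased per relative and r the share then answered correctly, with I for intervention and C for control:

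shift = 6.25 × (b_I × r_I − b_C × r_C).

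The article gives neither b nor r. For illustration only, take r_I = 0.90 (handouts at hand) and r_C = 0.40, with every blank chased:

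| Blanks, intervention | Blanks, control | Net items | Shift (points) |
|---|---|---|---|
| 1 | 1 | 0.90 − 0.40 = 0.50 | +3.1 |
| 2 | 2 | 1.80 − 0.80 = 1.00 | +6.25 |
| 4 | 4 | 3.60 − 1.60 = 2.00 | +12.5 |
| 1 | 2 | 0.90 − 0.80 = 0.10 | +0.6 |
| 1 | 3 | 0.90 − 1.20 = −0.30 | −1.9 |

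With these recovery rates the sign changes once control relatives leave more than 0.90 / 0.40 = 2.25 times as many blanks as intervention relatives. A course that works would itself leave fewer blanks in the intervention arm.

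**4. What a shift would do to the test.** The article gives no SD. Under the normal approximation (5% two-sided, 90% power), 12 per group implies 29 / ((1.960 + 1.282) × √(2/12)) = 21.9 points. I take 19.5 to 21.9 as an assumed range, and a design effect of 3.1 throughout. SE = SD × √(2 × 3.1 / n):

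- n = 44 per arm (one diabetes type): 7.3 to 8.2 points.
- n = 88 per arm (pooled): 5.2 to 5.8 points.

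With no true effect, a net half item (3.1 points) raises the two-sided rejection rate from 5% to about 7% per type and 8–9% pooled. A net whole item (6.25 points) raises it to about 12–14% and 19–23%. The rate is the same for a shift of equal size in either direction.

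**5. Baseline.** The rule covers all four assessments. A baseline blank chased after modules have begun could be answered with course knowledge. That would raise the intervention baseline, which the Limitations section relies on to control for earlier education, and it would work against the program.

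**The case against.** The case against has four parts.

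- **The rule does not name blank items.** It follows the sentence on postal invitations and precedes the one on drop-outs, and a request to contact and remind also fits people who have not attended or returned a form. This stands in part. However, gaps are noticed at data input, drop-outs have their own sentence and nothing is exempted, so item-level use is within the text without being stated.
- **The arms differ less than they seem to.** CDEs in both arms are trained before the study and centers hold the program materials, so a control CDE could prompt as well. This stands. What remains different is that intervention relatives have attended the course, hold its handouts and know the CDE as their teacher. The article describes no coaching.
- **A blank need not mean 'does not know'.** Response format, any don't-know option and weights are in additional files not shown. This stands, and it is why the point is worded as a possibility.
- **This is operational detail that an article may leave out.** That holds for sitting conditions and sealed envelopes. It does not hold for the retrieval rule, which the article states.

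A reader might infer that the rule biases the primary comparison towards the program by about a fifth of the target (6.25 / 29 = 0.22). The documents do not support that. The figure needs equal blanks in both arms, a 50-point gap in recovery and complete retrieval, none of which is given; other equally arbitrary inputs reverse the sign.

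**Conclusion.** The point holds as a weakness in a stated procedure; it is not a demonstrated bias. As written, the rule allows blank items on the relatives' primary endpoint to be completed after the sitting at the request of an unblinded person who, in one arm, taught the content. If it is used that way, it can distort the primary comparison.

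Direction and size are open. The only firm scale is 6.25 points for each net extra item filled correctly in one arm, against a target of 29 points, and even that assumes equal weighting. The rejection rates in the working also rest on an assumed SD and an assumed net excess. The conclusion itself needs only two things: that the rule reaches single items, and that a blank can carry information about knowledge. It justifies a cheap clarification and does not call the design into question.

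**What to change.** Add to Quantitative assessment: *Knowledge items left blank on a returned test are not queried and are scored as not correct, in both arms and at every assessment. CDE reminders are limited to wholly missing questionnaires and to items outside the knowledge test.*

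Trial status gives June 2019 as the end of participant recruitment and 25 July 2019 as the protocol version date. Baseline data were therefore collected under the existing rule, while the 6- and 12-month follow-ups of those recruited last lay ahead. For assessments already collected, flag retrieved knowledge answers where records allow and score them as not correct, at least in a sensitivity analysis, so that baseline and follow-up are handled alike.

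The cost is a clause in the data-handling instructions and a flag in the database. The downside is that some blanks that were oversights count as not correct, at 6.25 points each under equal weighting; this weighs more if the test offers a don't-know option. Completing the test in one sitting without course materials, and returning it in a sealed envelope, would help but is optional.
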